**Methods:**

The objective of the current pilot study is to explore the feasibility of a trial investigating the impact of computerized cognitive training, yoga, and an active control intervention (wellness education) in individuals with aMCI by conducting a group-randomized, multisite, parallel, three-arm pilot study. We will establish preliminary effect sizes regarding the association of each intervention with neuroimaging and cognitive and participant-reported measures. We also aim to estimate the strength of association between the various outcomes. The current trial aims to recruit 75 people with aMCI and their 75 cognitively healthy care partners through clinics and senior care facilities. The initial intervention will last 10 days and will consist of 1 h daily of the assigned intervention i.e., (yoga, computerized cognitive training, or wellness education) combined with 1 h of memory compensation training and 1 h of support groups. Twenty-five participants will be group-randomized to each arm using a random number generator. Study staff and participants will be kept blind until recruitment is complete for each group. After the initial two-week intervention, participants will continue the assigned intervention for 24 weeks. Outcome measures are: functional connectivity and cerebral perfusion as assessed by magnetic resonance imaging; cognition; daily functioning; mood; anxiety; self-efficacy; caregiver burden; quality of life; and study feasibility including recruitment and retention rates.

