## Methods

### Setting

Potential trial participants will be recruited from the Memory Disorder Clinics, behavioral neurology and neuropsychology practices at the University of Florida, Mayo Clinic Jacksonville, and Tallahassee Memorial Hospital. There will be three program sessions at each site. In order to reach target sample size, the trial will be advertised in healthcare and elderly living communities, at information sessions in the community, as well as by local healthcare professionals. We will also utilize advertising via brochures, flyers, newspaper articles, or other means suggested through the University of Florida, Mayo Clinic Jacksonville, and Tallahassee Memorial Hospital as appropriate. Medical providers may also refer patients with aMCI to the program.

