### Randomization and blinding

The group nature of intervention allows participants to compare their experiences, so individualized randomization poses a risk for diffusion of treatment effects. However, the group format limits in the ability to randomize per couple. Thus, we will block randomize by group instead of by participant assuring equal randomization of sessions to each of the three arms of the trial at each site. In other words, everyone in the first intervention period will receive the same treatment determined at random. The next intervention group will receive one of the two remaining arms also determined at random. The study biostatistician will randomize using a computerized random number generator to determine initial and second sessions at each site. The biostatistician is not involved in recruitment, assessment, or intervention delivery in any way. Due to the nature of the intervention, participants cannot be blinded. However, to mitigate selection bias, patients as well as study staff will be kept blind until recruitment for each session has been completed. Sessions will be offered sequentially three times in year 1 and include 6–12 individuals with aMCI and study partner couples per session. Hence, there will be the opportunity to block randomize nine (three sites × 3) sessions involving approximately 25 couples per arm for a total of 75 participants. A flow chart diagram showing summary of the pilot trial design can be found in Fig. 1.

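### Each site's third session gets its arm by elimination, so staff who know the first two arms are not blind while recruiting it

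*Protocol article*

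**What the plan says.** All of the following is in the Protocol article.

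- **Number of sessions.** Setting: "There will be three program sessions at each site".
- **Constraint.** Randomization and blinding: the plan is to "block randomize by group instead of by participant assuring equal randomization of sessions to each of the three arms of the trial at each site". With three sessions and three arms, each site receives each arm once.
- **Draws.** For the first session, "everyone in the first intervention period will receive the same treatment determined at random". Then: "The next intervention group will receive one of the two remaining arms also determined at random". The biostatistician's random number generator is used "to determine initial and second sessions at each site". No draw is described for the third session; it takes what is left.
- **Timing.** "Sessions will be offered sequentially three times in year 1 and include 6–12 individuals with aMCI and study partner couples per session". Intervention timeline adds that the nine groups start at different times.
- **Blinding of recruitment.** "patients as well as study staff will be kept blind until recruitment for each session has been completed". The Abstract repeats it: "Study staff and participants will be kept blind until recruitment is complete for each group".
- **Openness.** Randomization and blinding accepts that participants cannot be blinded to the treatment they receive.

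**The concern.** The blinding statement covers every session without exception, but the scheme in the same paragraph fixes the third arm at each site as soon as the second is known. The biostatistician's separation from recruitment does not help, because the third arm needs no access to the list; it follows from what the site has already run.

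With the third arm foreseeable, staff could, knowingly or not, hold a couple for that session or steer a couple away from it. That is the selection the blind is meant to prevent. It bears on two things the pilot is for. Aim 1C is to establish recruitment and retention rates, and the recruitment rate would mix concealed sessions with deducible ones. The effect sizes are meant to inform a larger trial, and they would rest partly on couples enrolled without effective concealment. The Discussion names only participants' awareness of their treatment as a limitation and offers the Treatment Diffusion Log against it. That log cannot address who was enrolled into which session.

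**Working it through.** **1. The plan's own figures.** 3 sites × 3 sessions = 9 sessions. 75 couples / 9 = 8.33 per session, inside the stated 6 to 12. 3 sessions per arm × 8.33 = 25 couples per arm. These agree with the article.

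**2. Predictability within a site.** Three arms used once each give 3! = 6 equally likely orders. The chance that someone who knows the arms already run at that site can name the next one is:

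| Session | Arms still possible | Best-guess probability |
|---|---|---|
| First | 3 | 1/3 |
| Second | 2 | 1/2 |
| Third | 1 | 1 |

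The third arm is certain in all 6 orders.

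**3. Extent.** One third session per site × 3 sites = 3 of 9 sessions. At the average size this is 3 × 8.33 = 25 of 75 couples. At 6 to 12 couples per session it is 3 × 6 = 18 to 3 × 12 = 36.

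**4. Would staff know the first two arms?** The intervention program section has study staff helping participants with the computerized training. Intervention timeline has staff following up missed yoga sessions, low training time and missing wellness logs, so their contact depends on the arm. Each group's programme lasts 2 + 24 = 26 weeks and three sessions are offered within a year, so staff will probably still be following an earlier group while the third is being filled. Nothing in the article separates recruiters from these staff, or closes third-session recruitment before the second arm is revealed.

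**5. Does the random order spread the exposure evenly over arms?** Assume the sites' orders are drawn independently. The three third-session arms then have 3³ = 27 equally likely combinations. All three arms appear in 6/27 = 22%. All three third sessions fall on one arm in 3/27 = 11%. So the exposure is uneven across arms with probability 1 − 6/27 = 78%.

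**6. Would independent draws be better?** They would hold the best guess at 1/3 for every session, but each site would keep one session per arm at all three sites with probability only (6/27)³ = 1.1%. The balance by site is worth keeping, so the remedy should lie in how couples are enrolled.

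**7. Effect of closing the last two sessions early.** If enrolment for a site's second and third sessions closes before the second arm is revealed, staff know only the first arm while recruiting both. The best guess is then 1/2 for each instead of 1/2 and 1.

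**The case against.** The strongest defence is that the scheme is described openly, that balance by site is a good reason for it, and that the exposure is limited. Much of this stands. The first session at each site is concealed, and at the second the arm is still unknown. The order is random within each site, so no arm is placed last by design, and the direction of any bias cannot be stated. The article gives no recruitment windows, so it is an assumption, though a natural one, that third-session recruitment is open after the second arm is revealed. None of this rescues a statement that applies to each session.

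A reader might infer more than the article supports:

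- **That couples enrol knowing their arm.** Prospective couples and outside referrers would know only if someone told them about the earlier sessions. The article does not say that anyone does. The point concerns site staff.
- **That baseline measures are taken with the arm known.** The blind is described as ending with recruitment, but the order of baseline testing is in the timeline and schedule figures, which were not available here. No conclusion can be drawn.
- **That predictability across the trial can be averaged into one figure.** An average would blend sessions where the arm is unknown with those where it is certain, and would overstate the problem.
- **That refusal is a compromised outcome.** The feasibility outcomes named are recruitment and retention; refusal is not among them.

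**Conclusion.** The blinding statement is wrong as written for the third session at each site: 3 of 9 sessions, about 25 of 75 couples, with a range of 18 to 36. For those couples the blind does not protect against selection at enrolment by staff who know the site's first two arms. It does hold for first sessions, and at second sessions it is weakened to a choice between two arms but not lost.

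This rests on two assumptions: that recruiting staff know which arms their site has run, and that third-session recruitment is still open when the second arm is revealed. The arm-specific follow-up by staff and the sequential sessions make both likely, and nothing in the article excludes either. The finding is that selection is possible. It does not show that selection occurred, or which arm it would favour.

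**What to change.** 1. **Correct the statement** in Randomization and blinding and in the Abstract: the third session at each site is not concealed from staff who know the earlier arms.
2. **Assign couples to sessions strictly in order of consent**, from a dated list held by someone independent of recruitment. Allow no movement between sessions at staff discretion, and log deferrals and declines by session. This limits steering; it does not make the third arm less predictable.
3. **Where scheduling allows, close enrolment for a site's last two sessions before the second arm is revealed.** This removes the cause. It needs about 2 × 8.33 = 17 couples enrolled at that point (12 to 24 at the stated session sizes), and third-session couples would wait longer. Where it is done, the correction in step 1 is not needed for that site.
4. **Report recruitment and baseline characteristics by session order, descriptively.** Do not use an analysis that drops the third sessions: it removes one arm from every site, and an arm from the whole trial with probability 3/27 = 11%.

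The cost is procedural wording, one list, and some loss of scheduling flexibility for couples. The balance of arms by site is unchanged. Recruitment was already under way when the article was submitted, so steps 2 and 3 can apply only to sessions not yet filled; steps 1 and 4 apply in any case.

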**Fig. 1 Fig1:**
[figure not shown]
*Flow chart* showing summary of the pilot trial design for the Physical Exercise And Cognitive Engagement Outcomes For Mild Neurocognitive Disorder (PEACEOFMND) Trial. Adapted from CONSORT Flowchart

### The intervention program

All participants in each arm of the intervention will receive memory compensation training and support groups in addition to the randomized intervention. During memory compensation training, the patient is trained to use a calendar and note-taking system in a consistent way in order to form calendar use habits [6, 7]. The use of the calendar is theorized to build primarily on procedural memory and priming, two types of implicit memory that remain relatively intact in aMCI. Separate support groups will be conducted with participants and study partners. A therapist will lead a discussion with regards to sharing disease-related experiences. There is no evidence to suggest and no theoretical reason to believe these compensatory/supportive interventions will impact the neuroimaging or cognitive measures in this trial. Even if they do, this effect should be balanced across the three arms of the interventions, as our active control group will also be receiving these treatments. In addition to these two “base” interventions, groups will be randomized to receive 60 min of daily yoga, computerized cognitive training, or wellness education. Each of these three interventions is described in more detail below:Yoga: Certified yoga instructors will use adapted hatha yoga where participants sit on armless chairs placed on sticky mats for some asana (poses) and use the chair for support throughout. This adapted hatha yoga style is appropriate for older adults including those who have limited mobility, use walkers, or are in wheelchairs. The appropriately sequenced yoga practice meets the American College of Sports Medicine recommendation for older adults for muscle strengthening and flexibility. Instructions are modeled for the participants.Computerized cognitive training: Use of a commercially available product, BrainHQ™, with scientific support for its efficacy in improving cognitive function. [20, 21]. We will use six validated modules from this program (Hawkeye, Divided Attention, Double Decision, Sound Sweeps, Syllable Stacks, and Memory Grid). Study staff will help participants with navigating the program. After the initial two-week intervention period, participants’ adherence and progress will be tracked through the computerized cognitive training portal.Active control (wellness education): In order to control for contact times and the calendar and support group interventions, controls will receive wellness education by licensed psychologists focused on the importance of diet, sleep hygiene, social engagement, and physical exercise delivered in a similar fashion to the other interventions.

### Intervention timeline

There will be nine different intervention groups, each starting at a different point in time. The initial intervention period will consist of 1 h daily of the assigned intervention (yoga, computerized cognitive training, or wellness education) in combination with 1 h of memory compensation training and 1 h of support groups. This will last for a period of ten days, delivered weekdays over two weeks. After the initial two-week intervention, participants will continue the intervention they were assigned to (yoga or computerized brain fitness) for another 24 weeks. Participants need to engage in the assigned intervention for at least 2 h for at least 20 out of 24 weeks to be considered a program completer. They are encouraged to do more. Attendance of the weekly yoga session as well as the number of minutes spent on yoga at home will be recorded each week. Individuals who miss a yoga session will be called by the study staff with the goals to record the number of minutes spent on yoga at home and will be encouraged to attend the next yoga session. For the computerized cognitive training arm, staff will track progress solely through the BrainHQ™ portal on a weekly basis. Individuals who spend < 120 min on computerized cognitive training will be contacted by the study staff and will be encouraged to spend more time on computerized cognitive training next week. The wellness education group will be asked to fill out and submit wellness logs for sleep, nutrition, and mood each week for 24 weeks. Individuals who do not send in their weekly log will be contacted via phone by the study staff and will be encouraged to send in their log next week. The amount of phone calls of the study coordinators to the participants will be recorded. Participants will not be restricted in concomitant care and interventions. A timeline chart from the perspective of participants is shown in Fig. 2.

**Fig. 2 Fig2:**
[figure not shown]
Participant timeline

### Discontinuation

Discontinuation of participants will occur upon participants’ request. If a participant discontinues, no new data on this participant will be collected.

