
#### Functional status

All measures of functional status will be conducted at baseline and after the six-month intervention period.The study partners will be asked to fill out the Everyday Cognition (E-Cog) [35] about the individuals with aMCI’s functioning in instrumental activities of daily living (IADLs). The E-Cog is an informant-based measure that assesses the participant’s ability to perform everyday tasks in the following areas: memory; language; visuospatial abilities; planning; organization; and divided attention.The study partners will be asked to fill out the Functional Assessment Questionnaire (FAQ) [36] about the person with aMCI’s functional status. The FAQ is the standard functional measure required for use throughout the Alzheimer’s Disease Research Center network.The study partners will be asked to fill out the Treatment Diffusion Log about the person with aMCI’s and their own time spent on any type of physical exercise, computerized cognitive training, wellness behaviors, use of a calendar, and supportive therapy. This will be done to assess specific skills targeted by the interventions.The Memory Compensation Training Therapists will fill out the MCT Adherence Questionnaire about the person with MCI’s use of the calendar. This questionnaire assesses how well an individual utilizes the sections of the MCT calendar system. The evaluator will examine MCT compliance for two randomly selected days from the prior week. This will be done on the first day of treatment, as well as during the booster session.The Memory Compensation Training Therapists will also be asked to determine the MCT Training Score on the final day of the program This 0–6 score reflects the individual with MCI’s progress in the three phases of calendar training. A score of 0 reflects no progress while a score of 6 reflects mastery of all three training phases. Intermediate scores (1–5) reflect intermediate levels of training progress.The Short Physical Performance Battery (SPPB) [37] will be administered to the individuals with aMCI to monitor their physical performance. This includes a timed 8-ft walk, standing side by side, semi-tandem and full-tandem stance, and a timed arms-folded rise from seated to standing.

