#### Quality of life, mood, and anxiety

The quality of life, mood, and anxiety measures will be conducted at baseline and after the six-month intervention period.Both the persons with aMCI and the study partners will be asked to complete the Quality of Life-AD (AD-QOL) [38] at baseline and after six months. The AD-QOL is a 13-item measure developed for individuals with dementia that has been utilized in aMCI and with study partners. Individuals with aMCI and study partners rate their relationships, concerns about finances, physical condition, mood, energy level, memory, aspects of daily functioning, and overall life quality on a four-point scale.Both individuals with aMCI and study partners will be asked to complete the Center for Epidemiologic Studies Depression Scale (CES-D), a well validated 20-item self-report measure of depressive symptoms with a four-factor structure consisting of negative affect, lack of positive affect, somatic symptoms, and interpersonal difficulties subscales [39].Both the persons with aMCI and the study partners will complete the REACH Anxiety Inventory Form (REACH-AIF) [40], a 10-item rating scale modified from the State-Trait Anxiety Inventory, by the Resources for Enhancing Alzheimer’s Caregiver Health (REACH) project [41].

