### Statistical methods

The primary analyses will use linear mixed effects models to examine change from baseline to post intervention (~ 6 months) in each of the outcomes. These models control for within-subject effects through the use of per-subject random effects for slopes and intercepts over the six-month follow-up period. We will estimate the degree of change over time in each of the specific measurement intervals within randomized groups and test for differences in these changes between groups while conforming to linear model assumptions. We will evaluate the assumptions required for the appropriate use of linear models and will apply any needed transformations in the data to conform to the model assumptions. Analyses will be conducted to assess the aims listed above. In addition, to make it possible to identify which individuals are most likely to benefit from the interventions, we will incorporate variables to evaluate whether variables either attenuate or modify cognitive or imaging changes. Additional analyses are currently unknown. Missing data will be handled based on what appears to be most appropriate for the analysis being conducted. No interim analyses will be conducted.

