### Harms

In this trial, we will use the Food and Drug Administration's definition of serious adverse events (SAEs) and adverse events (AEs). SAEs are unlikely in these behavioral interventions. Any SAE, whether or not it is related to the intervention, will be reported to the site Institution Review Board (IRB). The PI at each site will monitor for the presence of both SAEs and AEs at each scheduled visit. These individuals will report any SAE or AE to the overall PI twice a month. However, if the SAE involves death or a life-threatening event, the site PI will be notified within 24 h and the PI will notify the IRB within two working days from the time the SAE was first reported. Reports of SAEs received by the IRB will be reviewed by an institutional SAE board to determine the seriousness of the event and what actions, if any, will be required. In the event that a participant withdraws from the trial or the PI decides to discontinue a participant due to an SAE, the participant will be monitored by the site PI via ongoing status assessment until: (1) resolution of the problem is reached; or (2) the SAE is determined to be clearly unrelated to the trial intervention. Summary and outcome of all SAEs will be reported to the IRB annually.

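### The rule that stops all data collection at discontinuation does not separate stopping the activity from refusing assessment, and it is not reconciled with the follow-up described under Harms

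*Protocol article*

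**What the plan says.** The Discontinuation section has two sentences. The first gives the trigger: "Discontinuation of participants will occur upon participants’ request". The second gives the consequence: "If a participant discontinues, no new data on this participant will be collected". No exception is made for outcome data or for safety data, and the term is not defined.

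The Harms section covers the case in which a participant leaves, or "the PI decides to discontinue a participant due to an SAE". It says that "the participant will be monitored by the site PI via ongoing status assessment until" the problem resolves or the event is judged clearly unrelated to the intervention.

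On timing, the article says of one outcome family: "All measures of functional status will be conducted at baseline and after the six-month intervention period". For another it says: "The quality of life, mood, and anxiety measures will be conducted at baseline and after the six-month intervention period". Under Cognitive functioning, the DRS-2 and CogState are placed at the same two points. Statistical methods models change from baseline to about six months with linear mixed models. On missing values it says: "Missing data will be handled based on what appears to be most appropriate for the analysis being conducted".

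Non-adherence is handled separately, under Intervention timeline. Staff contact people who miss a yoga session, fall short on training minutes or do not send in a log, and encourage them to continue. Completing the program is a status of its own. Aim 1C is to establish recruitment and retention rates.

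**The concern.** Two events are folded into one word. A person can stop doing yoga or computer training and still be willing to be scanned, tested and interviewed. A person can also withdraw consent to all of that. The second properly ends data collection. The first need not, yet the rule as worded does not tell them apart.

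This matters more than usual because the main outcomes have a single planned follow-up. A discontinuer before six months leaves a baseline value and nothing after it. The mixed model can keep that baseline value, but it observes no change for that person.

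The pilot's products are effect sizes by arm (Aims 1A and 2) and a retention rate (Aim 1C), both meant to inform a larger trial. The 24-week demands differ by arm: weekly yoga sessions with home minutes recorded, 120 minutes a week of computer training, or weekly wellness logs. Loss that differs by arm and relates to outcome is therefore plausible, though the documents do not show that it will occur.

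The Harms section adds a textual problem. It names a trigger that the Discontinuation section does not mention, and it describes continued status assessment after discontinuation where the other section stops all new data.

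**Working it through.** **The passages side by side**

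| Question | Discontinuation | Harms |
|---|---|---|
| Who triggers it? | The participant, by request | The participant by withdrawing, or the PI because of an SAE |
| Is anything gathered afterwards? | No new data, no exception stated | Status assessment by the site PI until an end point |

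**The plan's own figures.** The plan gives no drop-out rate and no allowance for loss, so there is no figure on this point to reproduce. The yardstick used below is the effect size of 0.325 in the two Power and sample size paragraphs, with 118 per arm for 80% power. A one-sided α of 0.05 reproduces it: n = 2(1.645 + 0.842)² / 0.325² = 117.1, rounded up to 118. The point does not depend on this figure. The pilot itself is limited to 25 dyads per arm by funding.

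**Shift in one arm's observed mean.** Assumed inputs: a fraction q of one arm is lost, namely the lowest q on a latent tendency to stay, and that tendency correlates ρ = 0.3 to 0.5 with change. Among stayers the mean change, in SD units, moves by

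ρ · φ(z_q) / (1 − q)

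| q (assumed) | φ(z_q) | φ(z_q)/(1 − q) | ρ = 0.3 | ρ = 0.5 |
|---|---|---|---|---|
| 10% | 0.1755 | 0.195 | 0.06 | 0.10 |
| 20% | 0.2800 | 0.350 | 0.10 | 0.17 |
| 30% | 0.3477 | 0.497 | 0.15 | 0.25 |

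At 20% the unrounded shifts are 0.10498 and 0.17498. Divided by 0.325, these are 32% and 54%. Dividing a shift by q gives the implied gap between stayers and leavers: 0.105/0.20 = 0.52 SD and 0.175/0.20 = 0.87 SD.

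**Between arms.** What biases a comparison is the difference of the two arms' shifts.

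- With 20% lost in one arm and 10% in the other, it is 0.105 − 0.059 = 0.05 SD at ρ = 0.3, and 0.175 − 0.098 = 0.08 SD at ρ = 0.5.
- A second route uses share lost × (stayer mean − leaver mean). With 30% and 10% lost and leavers 0.5 SD worse: 0.30 × 0.5 − 0.10 × 0.5 = 0.10 SD, or 31% of 0.325.
- With 20% lost in both arms and the same 0.5 SD gap: 0.10 − 0.10 = 0 between arms, although each within-arm change is still off by 0.10 SD.

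**Precision.** The 95% half-width for a between-arm d is about 1.96 · √(2/n). With n = 25 it is 0.55. If 20% are lost, n = 20 and it is 0.62. Clustering by session, ignored here, would widen both.

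**The case against.** The strongest reply is that discontinuation, in a sentence about participants leaving at their own request, naturally means leaving the trial. On that reading, ending data collection is ordinary practice. The article supports this in part: Intervention timeline keeps people who miss sessions, minutes or logs in contact, and nowhere calls them discontinued. A reader might infer that everyone who falls short of the program-completer standard goes unassessed. The documents do not support that. The exposure is limited to people who ask to stop, and the fault is that the text does not say which kind of stopping it means.

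Second, the two sections may serve different purposes, one ending research data and the other following an SAE. That is possible, and the first section does not say that a request is the only trigger. But it states no safety exception and does not mention a PI decision, so the text needs reconciling. This is a gap in wording, not proof that safety follow-up would stop.

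Third, a missing single follow-up is not beyond recovery. Baseline values and the weekly adherence records could support a mixed model or multiple imputation under a missing-at-random assumption. A reader might infer that no method could help, which would be too strong. What stands is that the assumption cannot be tested from the data. The open sentence on missing data is not itself a fault, since such detail is commonly left to an analysis plan.

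Fourth, the size is illustrative. Drop-out and correlation are assumed, and sampling error with 25 per arm exceeds the shift. Both are true, but a shift from selection does not shrink when the pilot's estimates are carried into a larger trial.

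Finally, adherence is already recorded, so Aim 1C is not defeated. Those records allow intervention drop-out to be reported apart from assessment loss, if the plan says so. They cannot show how many people who stopped would have attended a visit to which they were not invited.

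**Conclusion.** The point holds as a fault of definition with a real consequence for the estimates. As worded, the rule can remove the six-month outcome of someone who stops the activity but would accept assessment. With two time points for the main repeated outcomes, that leaves no observed change for that person.

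The size rests on assumptions. At 20% loss in one arm only, with a correlation of 0.3 to 0.5, that arm's mean shifts by 0.10 to 0.17 SD. A reader might take the matching 32% to 54% of 0.325 as the bias in the trial's comparisons. It is not: it assumes no loss in the comparator, and the between-arm shift is about zero if loss and selection are equal. Nor is 0.325 an effect this pilot was sized to detect.

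The reading of the schedule rests on the article's text. The timeline and schedule figures are not shown, a few process measures such as the calendar-training score fall at other times, and the text gives no explicit time points for some memory tests.

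The Discontinuation and Harms sections differ on trigger and on later information, and must be reconciled. No view is taken here on which clinical follow-up rule is right. The change should be made, and it is a modest one.

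**What to change.** 1. In the Discontinuation section, define the term and limit the stop on data collection to participants who withdraw consent for assessment.
2. Invite participants who stop the intervention without withdrawing that consent to the six-month MRI, cognitive and questionnaire visit, and analyse them in the arm to which their session was randomized.
3. Under Aim 1C, report assessment retention (six-month data obtained) separately from intervention drop-out, using the attendance, portal and log records already planned.
4. Reconcile the Discontinuation and Harms sections on who can trigger discontinuation and on whether information is collected afterwards.

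The cost is protocol and consent wording, with IRB approval as the article's amendment section requires, and some added effort to arrange visits for people who have stopped the activity. The documents give no budget for those visits. Recruitment was still ongoing when the article was submitted, so a change at that stage could still have helped. Participants already consented may need to be told of it.
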